## Abstract

**Background:**

The rate of tobacco use among people with mental illness is nearly twice that of the general population. Psychotropic medications for tobacco cessation are relatively expensive for most Kenyans. Behavioral counseling and group therapy are effective lower cost strategies to promote tobacco cessation, yet have not been studied in Kenya among individuals with concomitant mental illness.

**Methods/design:**

One hundred tobacco users with mental illness who were part of an outpatient mental health program in Nairobi, Kenya were recruited and allocated into intervention and control groups of the study (50 users in intervention group and 50 users in control group). Participants allocated to the intervention group were invited to participate in 1 of 5 tobacco cessation groups. The intervention group received the 5As (Ask, Advise, Assess, Assist and Arrange) and tobacco cessation group behavioral intervention, which included strategies to manage cravings and withdrawal, stress and anxiety, and coping with depression due to withdrawal; assertiveness training and anger management; reasons to quit, benefits of quitting and different ways of quitting. Individuals allocated to the control group received usual care. The primary outcome was tobacco cessation at 24 weeks, measured through cotinine strips. Secondary outcomes included number of quit attempts and health-related quality of life.

**Discussion:**

This study will provide evidence to evaluate the efficacy and safety of a tobacco cessation group behavioral intervention among individuals with mental illness in Kenya, and to inform national and regional practice and policy.

**Trial registration:**

Trial registration number: NCT04013724.

Name of registry: ClinicalTrials.gov.

URL of registry: https://register.clinicaltrials.gov

Date of registration: 9 July 2019 (retrospectively registered).

Date of enrolment of the first participant to the trial: 5th September 2017.

Protocol version: 2.0.

## Background

Tobacco dependence is recognized as a mental and behavioral disorder in the International Classification of Diseases (ICD-10) of the World Health Organization (WHO) [1] and in the Diagnostic and Statistical Manual of Mental Disorders of the American Association of Psychiatry (DSM-V-TR) [2]. Patients with serious mental disorders have a greater prevalence of tobacco use [3], more severe psychiatric symptoms, poorer overall general well-being, and greater functional impairment when compared to non-tobacco users [4].

‘The likelihood that a person who smokes has a mental disorder is twice that of a person who does not have one’. [5, 6] The proportional relationship between the intensity of the psychiatric symptoms and the severity of the tobacco dependence has already been established [6, 7]. Tobacco-related illnesses including cancer, heart disease, and lung disease are among the most common causes of death among persons with mental illness. Globally individuals with serious mental illness and substance abuse on treatment in the public health system die, on average, 25 years earlier than those without mental illness [8].

According to World Health Organization (WHO), Quality of Life (QOL) definition is individualistic, has a cultural and value systems dimension in relation to the persons goals, expectations, standards and concerns. WHO recognizes 5 domains that should be captured while assessing quality of life: Physical, Psychological, social, environmental, and spiritual [9]. With the rate at which a person with mental illness smokes, they are more likely to suffer from the physical domain, due to the health impact of tobacco use. QOL has been said to involve two dimensions – adaptive functioning (self-care and social roles) and life satisfaction or subjective wellbeing [10]. Most people with mental illness need support to balance their emotional and physical needs.

Randomized controlled trials have shown that tobacco cessation treatment among patients receiving concomitant mental health treatment is effective and safe, does not exacerbate mental health symptoms, and does not lead to increased use of alcohol or illicit drugs [11–13]. However, most research on the efficacy and safety of tobacco cessation interventions has excluded participants with a past or present history of mental illness; thus, this population has remained underrepresented in randomized trials of tobacco cessation intervention strategies [14].

Morris et al. [15] found that most mental health providers receive little or no training on smoking cessation and frequently have misconceptions, such as that patients with mental illnesses need to use tobacco to control their psychiatric symptoms and that these individuals have no desire to quit. A 2013 Cochrane systematic review [16] demonstrated how myths have led to persistently high tobacco use among the mentally ill, including myths that persons suffering psychological disorders lack motivation for tobacco cessation, that individuals with mental illness do not have the capacity to quit and that efforts to quit may actually impede their mental health treatment. Because of this misinformation, lack of awareness and smoking cessation interventions competence, tobacco use among this special group has been overlooked, depriving mental health patients of the necessary interventions for its control and prevention [17].

Few studies have focused on group behavioral interventions without addition of pharmacotherapies among this group, and few, if any, of these studies have been performed in Africa. In Kenya, there is limited access to tobacco cessation pharmacotherapies, which are also not affordable to most of this population. Because of the need, this study sought to evaluate the efficacy and safety of a group tobacco cessation behavioral intervention among patients with mental illness who attend outpatient programs at Mathari Referral and Teaching Hospital in Nairobi.

### Objectives

To determine the efficacy and safety of a group tobacco cessation behavioral intervention among tobacco using patients with mental illnesses on tobacco cessation at 6 months.To evaluate the impact of tobacco cessation on health-related quality of life of patients with mental illnesses.

## Methods/ design

### Study design

This study used a controlled clinical trial design.

### Study setting

This study was conducted at Mathari Referral and Teaching Hospital Clinic for Substance Abuse Treatment (CSAT) and outpatient follow-up clinics. Mathari Referral and Teaching Hospital is Kenya’s only national referral and teaching psychiatric hospital with a capacity of 700 beds. The staff who provide services at the hospital include 243 nurses, 7 psychiatrists (2 of whom are full-time administrators), 2 pharmacists, and support staff. Tobacco cessation therapy was provided by trained tobacco cessation counsellors. The study was conducted at the CSAT and other outpatient clinics.

### Sample size calculation [18]

The sample size necessary for comparing proportions includes: proportion *p*_*1*_ being the estimated proportion of study participants with improved health status after the intervention and *p*_*2*_ being the estimated proportion of study participants with improved health outcomes in the control group.

$$ n=\left(\frac{r+1}{r}\right)\;\frac{\left(\overline{p}\right)\;\left(1-\overline{p}\right)\;{\left({Z}_{\beta }+{Z}_{\alpha /2}\right)}^2}{{\left({p}_1-{p}_2\right)}^2} $$

**Table Taba:** 

Ratio of intervention: controls (r)	1
Estimated proportion with improved outcomes in intervention group p_1_	35.0%
Estimated proportion with improved outcomes in control group p_2_	15.0%
Odds Ratio	3.05
Average of proportions (p_1_ + p_2_)/2	0.25
Power (1-α/2)	95%
Power (1-β)	80%
Sample size per group	37
Sample size per group after adjusting for 30% attrition rate	48
**Total sample size**	**96**

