### Baseline and follow-up assessments

During baseline, Age of first use, duration of use, amount used, mental illness managed, Fagerstrom test score, and other substances used were documented. During weeks 4, 12 and 26, Quit attempts made, amount currently being smoked and Cotinine test results were documented. During week 26, the WHOQOL questionnaire was re-administered.

Based on previous tobacco cessation intervention trials, it was assumed that those who did not report abstinence had positive cotinine results.

At the group assessments (Weeks 4, 12, and 26), participants who reported continued tobacco use abstinence and consented to a saliva test were tested using a nicotine cotinine strip (Devon Medical: Nicotine/tobacco test kit). The saliva tests were evaluated by the nurses working at the hospital who were blinded to treatment allocation and were not otherwise part of the study.

The summary of the follow-up assessment activities is reported in Table 2.

**Table 2 Tab2:** Baseline, Follow-up activities and Data to be collected summary

Follow-up time	Activity	Documentation
Week 0 (Baseline)	• Socio-demographic questionnaire • Fagerstrom test for nicotine dependence • WHO quality of life (QOL) instrument	• Age of first use, duration of use, amount used, mental illness managed, other substances used • Fagerstrom test score • WHO QOL score
Week 4	• Explored progress made and documented quit attempts • Focused on challenges experienced and how they were managed • Documented number of sticks currently smoked • Those reporting complete cessation and who gave consent for saliva testing, were then screened using cotinine test	• Quit attempts made • Amount currently being smoked • Cotinine test
Week 12	• Explored progress made and documented quit attempts • Focused on challenges experienced and how they were managed • Documented number of sticks currently smoked • Those reporting complete cessation and who gave consent, were screened using cotinine test	• Quit attempts made • Amount currently being smoked • Cotinine test
Week 26 (Final follow-up)	• Explored progress made and documented quit attempts • Focused on challenges experienced and how they were managed • Documented number of sticks currently smoked • Those reporting complete cessation, gave consent, then were screened using cotinine test • Administered WHO QOL instrument	• Recorded quit attempts made • Amount currently being smoked • Cotinine test • WHO QOL score

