### Outcome measures

The study’s primary outcome was self-reported continuous tobacco use abstinence, biochemically verified, at Week 26. It was estimated that the intervention would increase tobacco cessation from the current rate of 15 to 35% [21]. While adjusting for 30% attrition rate, with a sample size of 48 per group, 96 participants would provide 80% power to detect this between-group difference with a two-sided alpha = 0.05.

Secondary outcomes assessed included cessation at Week 4 and 12, number of quit attempts, reduction in number of cigarettes used per day, and health-related quality of life measured at Week 26.

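### The 30% attrition step does not support the stated 80% power: it multiplies by 1.3 instead of dividing by 0.7, and the plan does not say whether dropouts count as smokers

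*Protocol article*

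**What the plan says.** In the Protocol article, the table under Sample size calculation takes 35.0% for the intervention group ("Estimated proportion with improved outcomes in intervention group") and 15.0% for the control group ("Estimated proportion with improved outcomes in control group"). It gives 37 per group, then 48 in the row "Sample size per group after adjusting for 30% attrition rate", and a total of 96.

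Outcome measures repeats this as a statement of power: "While adjusting for 30% attrition rate, with a sample size of 48 per group, 96 participants would provide 80% power", at two-sided alpha 0.05. The same section describes the effect as "the intervention would increase tobacco cessation from the current rate of 15 to 35" percent. It does not say whether these are rates among people followed to Week 26 or among everyone enrolled.

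Baseline and follow-up assessments gives the only rule on scoring people without a verified result: "it was assumed that those who did not report abstinence had positive cotinine results". It does not mention missed visits or loss to follow-up.

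The Abstract and Recruitment sections report that 100 people were enrolled, 50 per group.

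**The concern.** There are two problems in one row of the table.

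The first is the operation. Adding 30% to the required number is not the same as allowing for a 30% loss, because the loss applies to the larger number enrolled.

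The second is the denominator. Enlarging n while leaving both rates alone is valid when those lost leave the analysis. If they stay in as smokers, the rates themselves fall, the difference narrows, and a larger n chosen for the original difference no longer gives the intended power. If the rates already count those lost as smokers, no enlargement is called for. The scoring rule and the attrition row therefore need a common statement of who is in the denominator, and the article does not give one.

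What is at stake is how the result is read. Anyone relying on the stated 80% would take a non-significant result as stronger evidence against the intervention than this trial can provide.

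**Working it through.** **Inputs.** Rates of 35% and 15%, ratio 1 and 30% attrition come from the sample size table. Two-sided alpha 0.05 and 80% power come from Outcome measures. The 50 per group comes from the Abstract. Equal attrition in both arms and independent participants are assumptions made here.

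**Formula as printed.** n = ((r+1)/r) × p̄(1−p̄)(Zβ + Zα/2)² / (p1−p2)². Solved for power with r = 1: power = Φ( |p1−p2| / √(2p̄(1−p̄)/n) − 1.96 ).

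**The plan's base figure.** With p̄ = 0.25 and Z values 1.96 and 0.84: 2 × 0.1875 × 7.84 / 0.04 = 73.5 (73.6 with unrounded Z values), so 74 per group. The printed 37 appears only when the factor (r+1)/r = 2 is omitted (36.8). That is a separate error, noted because it affects every power figure below.

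**The plan's attrition figure.**
- 37 × 1.3 = 48.1, which reproduces the printed 48.
- 37 / 0.7 = 52.9, so 53 are needed to keep 37 completers.
- 48 × 0.7 = 33.6 completers, fewer than the table's own 37.

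**The three readings with 50 per group.**

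| Reading | Rates compared | n per group | Power |
|---|---|---|---|
| Those lost count as smokers; 35%/15% are rates among those followed | 0.7 × 35% = 24.5% vs 0.7 × 15% = 10.5% | 50 | Φ(0.14/√(2 × 0.175 × 0.825/50) − 1.96) = Φ(−0.118) = 45% |
| Those lost leave the analysis | 35% vs 15% | 50 × 0.7 = 35 | Φ(0.20/√(0.375/35) − 1.96) = Φ(−0.028) = 49% |
| 35%/15% already describe everyone allocated | 35% vs 15% | 50 | Φ(0.20/√(0.375/50) − 1.96) = Φ(0.349) = 64% |

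Exact enumeration of the uncorrected chi-squared test gives 47% for the first row and 65% for the third, so the approximation is not the source of the shortfall.

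**What correcting the base number would and would not repair.** Take 74 per group and divide by 0.7, giving 106 enrolled.
- Those lost count as smokers, rates among those followed: the difference is 14 points rather than 20, and power is about 77%. Reaching 80% at 24.5% vs 10.5% takes 2 × 0.144375 × 7.849 / 0.0196 = 115.6, so 116 per group.
- Those lost leave the analysis: about 74 completers remain and power is 80% to 81%.
- Rates already describe everyone enrolled: power is 92% to 93%, and the enlargement was unnecessary.

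**Sensitivity to the attrition rate.** Under the first of these three readings with 106 per group, power is 83% at 20% loss and 89% at 10% loss. With 50 per group and 20% loss it is about 52%.

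**The case against.** The scoring sentence sits among the cotinine procedures, directly before the statement of who was offered a saliva test. It can be read as covering only attendees who admitted smoking and so were not tested. On that reading those lost leave the analysis, and allowing for attrition is right in principle. Other text is compatible with this: Limitations of the study says participants with severe withdrawal were discontinued, and Data management and analysis plans Kaplan-Meier and Cox analyses, in which people lost would ordinarily be censored. Detailed handling of missing outcomes may also sit in an analysis plan that is not shown.

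This objection stands as far as it goes. A reader might infer that the article definitely counts dropouts as smokers, and that 80% power therefore fails even with a correct base number. The documents do not support that. The rule does not name dropouts, and nothing says that 35% and 15% are rates among those followed. If they already apply to everyone enrolled, nothing is diluted.

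It is also fair that the part of the shortfall due to dilution alone is modest, about 3 points (77% against 80% with 106 per group), and that it disappears at 20% attrition.

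The objection does not rescue the printed figures. Even when attrition is properly allowed for, the operation used is the wrong one. And the article itself states 80% power after attrition, so that claim can be checked without an analysis plan.

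**Conclusion.** The point holds in a conditional form. The move from 37 to 48 is wrong as an allowance for 30% loss: 53 would be needed. The 80% in Outcome measures is not reached with 50 per group on any of the three readings: about 45%, 49% or 64%. Which figure applies cannot be settled from the article, because it does not say how those lost are counted or which population the two rates describe.

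The size has two sources. The fall from 80% to 64% comes from the base number (37 instead of 74) and would exist with no attrition at all. The further fall to 49% or 45% comes from attrition under the respective reading.

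The figures rest on 30% loss in each arm. Under the reading in which those lost count as smokers, unequal loss matters: with 50 per group, 40% loss in the intervention arm and 20% in control gives about 23%, and the reverse gives about 69%. No allowance is made for recruitment and allocation in batches of 10.

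**What to change.** Make these changes in the sample size table and in Outcome measures, without enrolling more participants:

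1. State whether people lost before Week 26 count as smokers in the primary comparison, and align the sentence in Baseline and follow-up assessments with that choice.
2. State whether 35% and 15% are rates among those followed or among everyone allocated.
3. Replace the attrition row and the 80% sentence with the power at 50 per group for the chosen reading: about 45% (24.5% vs 10.5%, all allocated), about 49% (35% vs 15%, 35 completers per group) or about 64% (35% vs 15%, all allocated, no attrition enlargement).
4. Add that the figure assumes equal 30% attrition where attrition enters, that it makes no allowance for the batches of 10, and that much of the gap from 80% comes from the base number of 37 instead of 74.

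The cost is a few lines of text and calculation and a less favourable printed power. Follow-up is already complete, and no procedure changes.

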### Inclusion criteria

18 years of age and above.History of tobacco use for more than 6 months.A Fagerstrom score of 6 and above, which is a threshold consistent with dependence [17].Currently on outpatient follow up treatment for a diagnosed mental health condition.Willing to be part of the study for 6 months.

### Exclusion criteria

Patients on nicotine replacement therapy (NRT) or other pharmacotherapy for tobacco cessation.Patients currently experiencing severe psychotic episodes judged by their treating health care provider.Patients who would not be able to commit to the group sessions, defined as those who would not be able to attend group sessions for any reason, including transport-related reasons.

### Recruitment

Prior to recruitment, YO trained 2 counsellors or nurses who assisted with recruitment, screening, intake, and registration. Three addiction therapists who did not work at the hospital were trained by YO to lead tobacco cessation groups tailored to psychiatric patients. All patients who were enrolled for follow-up programs at CSAT and follow-up clinics were asked about their history of tobacco use by the intake/registration nurses.

All patients who walked in for follow-up after hospital discharge for a primary mental health diagnosis were informed of the study and were invited to participate. Informed consent was obtained from individuals who had capacity to provide informed consent in the presence of the clinicians working with the participants to ensure they understood the study requirements. Individuals who did not have capacity to provide informed consent were not recruited to minimize potential risks to this vulnerable population. After providing informed consent, participants were asked to complete the Fagerstrom tobacco use test. Participants were then asked to complete sociodemographic questionnaire and the World Health Organization (WHO) quality of life questionnaire. This screening and recruitment continued until the number of participants who provided informed consent reached 100.

### Randomization/allocation

Participants were recruited in clusters of 10 for allocation into the intervention and control groups. The first 10 participants formed group 1, and the next 10 participants formed group 2. Group 1 became the first intervention group, while group 2 became the first control group. This procedure continued until all 10 groups were formed (5 intervention and 5 control groups).

Participants were followed up clinically for ongoing mental health care on their regular clinic days.

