### Study intervention

5As-based brief advice was offered to the intervention group participants by the study team who were trained by YO. This brief advice consisted of an individual session lasting approximately 5 min for each participant immediately after their consent had been obtained. The focus of the 5As was to enable the therapist know the immediate concern of each participant and to enable adequate support when the particular issues were raised during the group intervention sessions. The behavioral group intervention consisted of 6 sessions over 12 weeks and were led by 2 trained facilitators, followed by monthly group meetings from weeks 14 to 26. This program was adapted from the Royal Australian College of General Practitioners’ *Supporting Smoking Cessation Guide for Health Professionals* [19] and the World Health Organization’s *Strengthening Health Systems for Treating Tobacco Dependence in Primary Care* training package [20].

The topics that were explored during the group sessions include:
Introduction to the Program and Reasons to QuitBenefits of Quitting and Understanding Why We Smoke and Ways of QuittingWithdrawal Symptoms and Social SupportDealing with Stress and Anxiety and Coping with Depression due to withdrawalAssertiveness Training and Anger ManagementTobacco-Free Lifestyle and Dealing with High Risk Situations

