### Control group procedures

The control group was provided questionnaires to fill at the end of Weeks 4, 12, and 26. During the rest of the study, they continued receiving usual care, including clinical care at CSAT. After the conclusion of the study, the control group will be offered the group sessions that the intervention group received.

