During exploratory data analysis, discrete variables will be summarized using frequencies and percentages, while continuous variables will be summarized using measures of central tendency and dispersion such as means with standard deviations and median with inter-quartile ranges, where appropriate. Bivariate analysis will be carried out to compare the intervention groups with the control groups with respect to socio-demographic characteristics, history of tobacco and substance abuse, type(s) of mental illness, and WHOQOL-100 scores at baseline. Mann Whitney tests will be employed to compare the intervention and control groups where predictor variables are continuous, and chi-squared tests will be applied when the predictor variable is categorical. We will compare unadjusted and adjusted cessation rates at 6 months, recognizing the limitations of the study design at eliminating potential confounders between the two groups given the non-randomized nature of group allocation. Potential confounders include age, sex, baseline tobacco, and baseline type of mental illness, among others. Time to cessation of tobacco use will be compared between the two groups by creating Kaplan-Meier curves and with the creation of corresponding Cox proportion hazard models to determine the effect of the intervention on the primary study outcome. We will report unadjusted and adjusted models, the latter which will aim to control for independent factors associated with relapse. We will perform similar analyses for secondary outcomes as well. All analyses will be carried out using IBM SPSS Statistics Software Version 24, and a two-sided *p* < 0.05 will be used to determine statistical significance.

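### Allocation is by whole batch of 10, but the named analyses and the sample size treat participants as independent, so p-values are too optimistic if outcomes within a batch are correlated

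*Protocol article*

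**What the plan says.** Under Randomization/allocation the protocol article says: "Participants were recruited in clusters of 10 for allocation into the intervention and control groups". Batches are formed from consecutive recruits and alternate between arms: "Group 1 became the first intervention group, while group 2 became the first control group". This continues until there are five batches per arm. No participant is allocated individually.

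The intervention arm is also treated in groups. The abstract says: "Participants allocated to the intervention group were invited to participate in 1 of 5 tobacco cessation groups". The Study intervention section adds: "The behavioral group intervention consisted of 6 sessions over 12 weeks and were led by 2 trained facilitators", with monthly group meetings afterwards. Controls have no group sessions during the study. Apart from questionnaires at weeks 4, 12 and 26, "During the rest of the study, they continued receiving usual care, including clinical care at CSAT".

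The Data management and analysis section compares the arms with Mann-Whitney tests for continuous variables and says "chi-squared tests will be applied when the predictor variable is categorical". It plans unadjusted and adjusted cessation rates at 6 months, and Kaplan-Meier curves "with the creation of corresponding Cox proportion hazard models to determine the effect of the intervention on the primary study outcome". Similar analyses follow for secondary outcomes, all judged at two-sided p < 0.05. The confounders it lists are individual characteristics. It recognises confounding from non-random allocation, but mentions no ICC, design effect, random effect, frailty, robust variance or batch-level comparison. The sample size formula is the one for two independent proportions.

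**The concern.** When whole batches are assigned, the difference between arms has to be judged against the variation between batches. There are 10 batches, which leaves 8 degrees of freedom for that comparison, whereas an individual-level comparison of 100 people would have about 98. People in one batch share a recruitment window. In the intervention arm they also share group discussion, which the article itself counts as a strength. Correlated outcomes within a batch are therefore plausible.

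If that correlation is positive, methods that assume independence give standard errors that are too small, and the 0.05 threshold no longer delivers a 5% error rate. Adjusting for age, sex, baseline tobacco use and diagnosis addresses imbalance, but it does not put batch into the variance. At stake is a false claim of efficacy from a trial intended to inform national and regional practice.

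**Working it through.** **1. The plan's own figure.** Inputs from the Sample size calculation section: p1 = 0.35, p2 = 0.15, mean 0.25, ratio 1, 80% power, two-sided alpha 0.05. The printed formula gives

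n = 2 × 0.25 × 0.75 × (0.842 + 1.960)² / 0.20² = 73.6, so 74 per group.

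The article prints 37. Leaving out the factor (r+1)/r = 2 gives 36.8, so 37, and 37 × 1.3 = 48.1 gives the printed 48. This is a separate error. It matters here because power under independence is already only about 64% with 50 per arm, before clustering is considered.

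**2. Design effect.** Batch size m = 10 and 5 batches per arm (Randomization/allocation). The ICC is an assumption, shown as a range.

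- Both arms clustered: DE = 1 + 9 × ICC.
- Intervention arm only: mean variance inflation (DE + 1)/2.
- Approximate type I error of a nominal 5% test: 2 × [1 − Φ(1.96/√inflation)].

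These were checked by beta-binomial simulation: 5 versus 5 batches of 10, true rate 15% in both arms, 200,000 runs, uncorrected chi-squared test.

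| ICC | DE | Effective n (100/DE) | Both arms: formula / simulated | Intervention arm only: formula / simulated |
|---|---|---|---|---|
| 0 | 1.00 | 100 | 5.0% / 5.5% | 5.0% / 5.6% |
| 0.01 | 1.09 | 92 | 6.1% / 6.5% | 5.5% / 6.1% |
| 0.02 | 1.18 | 85 | 7.1% / 7.6% | 6.1% / 6.5% |
| 0.05 | 1.45 | 69 | 10.4% / 11.0% | 7.7% / 8.2% |
| 0.10 | 1.90 | 53 | 15.5% / 16.3% | 10.4% / 11.0% |

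The simulated 5.5% at ICC 0 is a small-sample feature of the chi-squared test and is not clustering. A t-test on the 10 batch proportions (8 df) gave 4.5% to 5.7% over these ICCs in both settings.

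**3. Power of the batch-level t-test.** Assume 15% versus 35% and all 100 analysed. The standard error is √[(0.35 × 0.65 + 0.15 × 0.85) × DE / 50] = √(0.0071 × DE), the noncentrality is 0.20 divided by that, and the critical t on 8 df is 2.306.

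| ICC | Noncentrality | Power, noncentral t | Power, simulated (both arms) |
|---|---|---|---|
| 0 | 2.37 | – | 55% |
| 0.02 | 2.19 | 48.5% | 48.7% |
| 0.05 | 1.97 | 41.1% | 41.7% |
| 0.10 | 1.72 | 32.9% | 33.6% |

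With clustering in the intervention arm only, the simulated figures are 50%, 45% and 36% at ICC 0.02, 0.05 and 0.10.

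**4. Where the loss comes from.** Power goes from the stated 80% to about 64-65% because 50 per arm are available where the formula needs 74. It falls to 55% because 8 df replace an individual-level test. Only the step below 55% is due to the ICC.

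**The case against.** The strongest reply has five parts.

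- **Controls are not treated in groups.** A reader might infer that both arms are treated in batches. The Control group procedures section does not support that: controls receive usual care and share only recruitment order at one hospital. This stands. The intervention-arm-only column is therefore needed as the milder case, and it still shows inflation.
- **The ICC is unknown.** This also stands. It cannot be said that standard errors are certainly too small, only that they are for any positive ICC. At ICC 0.01 the type I error is about 6% or slightly more.
- **Chi-squared is not expressly assigned to week 26 cessation.** Its sentence follows the baseline comparisons. The model tied by name to the primary outcome is Cox, whose inflation was not simulated. The percentages above should not be read across to it, although a standard Cox model makes the same independence assumption. The article also sets a p-value threshold and says nothing of confidence intervals, so the remark on intervals concerns those derived from the named models.
- **Shared facilitators prove nothing.** One might infer correlation from a common pair of facilitators. If the same people led every intervention group, their effect is common to the arm and adds no variance between batches. The article does not say how facilitators were assigned to groups.
- **An unseen analysis plan may deal with it.** This carries little weight. The article fixes the tests, the confounders and the threshold, and discusses the allocation method only as a source of confounding.

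**Conclusion.** The named analyses and the sample size do not match a design that allocates 10 whole batches. For any positive ICC, p-values and intervals from them are too optimistic. For a chi-squared comparison of week 26 cessation, the type I error is about 7-8% / 11% / 16% at assumed ICCs of 0.02 / 0.05 / 0.10 with both arms clustered, and about 6-6.5% / 8% / 11% with the intervention arm alone. These figures rest on the assumed ICCs, equal batches of 10, no attrition and a 15% rate under the null.

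A reader might blame clustering for the whole distance between the stated 80% power and 33-49%. The working does not support that. Power is already about 55% at ICC 0, because of the sample-size error and the small number of batches.

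**What to change.** - Carry batch number (1 to 10) as an analysis variable.
- Make the primary week 26 comparison one of two prespecified options. The first is a mixed logistic model with a random batch intercept, small-sample degrees of freedom and the confounders the analysis section already lists. The second is a t-test on the 10 batch proportions (8 df), preferably covariate-adjusted, since a plain t-test would drop the adjustment that the plan promises.
- For time to cessation, use Cox models with batch-robust variance or shared frailty, and interpret them cautiously with only 10 batches.
- Treat the secondary outcomes in the same way.
- Report the estimated ICC with its uncertainty, and restate power with a design effect, separately from correcting the 37 per group.

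The cost is analysis wording and one variable already known from allocation. No new data are needed, and at the time of the article follow-up was complete with results still awaited. The price is wider intervals and a lower stated power.
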